### 3.2.2 Phase II

Primary endpoint:

- to evaluate the overall response rate (ORR, consisting of: CR, CRp and CRi as defined by IWG criteria) of the whole study population

Secondary endpoints:

- to compare the ORR rate of the Flt3-mutated patients versus the Flt3-wildtype patients and within different cytogenetic risk groups
- to evaluate the CR rate of the whole study population
- to compare the CR rate of the Flt3-mutated patients versus the Flt3-wildtype patients and within different cytogenetic risk groups
- to evaluate the one-year overall survival (OS) of the whole study population

---

 response criteria by the International Working Group (IWG) are defined as:

- Complete remission (CR): less than 5% bone marrow blasts and regeneration of both peripheral neutrophils to  $>1,000/\mu\text{l}$  and platelets to  $>100,000/\mu\text{l}$
- Complete remission with incomplete platelet recovery (CRp): less than 5% bone marrow blasts and regeneration of peripheral neutrophils to  $>1,000/\mu\text{l}$  with a platelet count of  $<100,000/\mu\text{l}$
- Complete remission with incomplete neutrophil recovery (CRi): less than 5% bone marrow blasts with a neutrophil count of  $<1,000/\mu\text{l}$  with or without platelet recovery

- to compare the one-year overall survival (OS) of the Flt3-mutated patients versus the Flt3-wildtype patients and within different cytogenetic risk groups
- to evaluate the relapse-free survival (RFS) of the responding patients
- to evaluate the time to response (CR, CRp or CRi) of the responding patients
- to evaluate the toxicity in the whole study population
- to evaluate the development of biomarkers indicating the course of disease, including genetic, epigenetic, transcriptional, protein and phosphoprotein markers in leukemic blasts, bone marrow, peripheral blood cells, serum and plasma, and bone marrow microvessel density.

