## 5.4 Study treatment overview

### 5.4.1 Treatment and observation

Patients will receive low-dose cytarabine in a dose of 20 mg as subcutaneous injection twice daily on days 1-10 of each cycle and BIBF 1120 twice daily (for dose level, see below) as an oral dose throughout the cycle on a 28-day cycle. A bone marrow aspirate and a complete blood count (CBC) with differential blood count for response evaluation will be performed between days 24 and 28 of each cycle. Patients will receive additional cycles from day 29 on for up to six cycles in total if the following applies: I. absence of significant disease progression as judged by the investigator, II. absence of unacceptable toxicity, and III. no adequate response (CR, CRp or CRi) in the bone marrow evaluation between days 24 and 28. The application of the next therapy cycle can be postponed for up to 28 days (up to day 57) due to the following reasons: A) the application of cytarabine on day 29 is undesirable in the opinion of the investigator, B) I. and II. applies and the result of the response assessment is pending when the next cycle is due, or C) I. and II. applies and the response assessment could not be performed\* (i.e., reduced general condition, infectious complications) or was not evaluable\* (i.e., no aspirated bone marrow spicules). Under these circumstances, patients will be bridged to the next cycle with BIBF 1120 at the last dosage of the previous cycle. In case of the achievement of a CR, CRp or CRi, or in case of no evaluable response by day 57, patients switch to observation. In case of progressive disease (for definition of leukemia progression see the asterisk on the following page) or intolerable toxicity, patients will be observed for survival (see 5.4.2 and 5.4.3).

- \* In these cases, bone marrow aspiration will be postponed / repeated together with physical examination, vital signs and body weight (see 6.2, table 2 for details). These bone marrow results have to be available by day 57 at latest. A core biopsy is recommended in a repeat bone marrow biopsy in case of an initial dry tap.

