## 8 STUDY OUTCOME AND STATISTICAL ANALYSIS

### 8.1 Power and Sample Size Calculation

In phase II of the study the primary endpoint is the overall response rate (ORR) in the whole study population. In the primary analysis the following null hypothesis will be tested against a one-sided alternative on the significance level  $\alpha=0.025$ .

$H_0$ : ORR $\leq$ 25% versus  $H_1$ : ORR $>$ 25%

The ORR under BIBF 1120 treatment is expected to depend on the absence or presence of a Flt3-mutation. In Flt3-mutated and Flt3-wildtype patients the expected ORR is ORRFlt3-mutated=50% and ORRFlt3-wildtype=35%, respectively. In present data of a comparable population 13% of study patients showed a Flt3-mutation. Thus across all study patients the expected ORR amounts to  $ORR = 50\% \cdot 0.13 + 35\% \cdot 0.87 = 37\%$ . A single stage design with fixed sample size was chosen. Given the above expected ORR=37%, in order to provide a  $1-\beta=80\%$  power of the primary hypothesis test, 111 evaluable patients are required to be included in the study, i.e. expectedly 14 Flt3-mutated and 97 Flt3-wildtype patients. 11 patients (10%) are anticipated not to be evaluable in the primary analysis due to missing data. Thus a total of 122 patients will be recruited into the phase II part of study.

Power calculations were performed using SAS version 9.2 (SAS Institute Inc., Cary, NC, USA).

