##### Responding Patients:

Morphologic complete remission (CR):

- Platelet count >100,000/ $\mu$ l
- Granulocyte count of >1,000/ $\mu$ l
- Bone marrow (aspirate with marrow spicules): < 5% blasts, Absence of Auer rods
- No evidence of persisting leukemia by flow cytometry (Sensitivity: 5%)
- Absence of extramedullary leukemia
- Transfusion independent stable hemoglobin value

Complete remission with incomplete platelet recovery (CRp):

- Granulocyte count of >1,000/ $\mu$ l
- Bone marrow (aspirate with marrow spicules): < 5% blasts, Absence of Auer rods
- No evidence of persisting leukemia by flow cytometry (Sensitivity: 5%)
- Absence of extramedullary leukemia
- Peripheral blood with no blast cells and less than 100,000/ $\mu$ l platelets

Complete remission with incomplete neutrophil recovery (CRi):

- Bone marrow (aspirate with marrow spicules): < 5% blasts, Absence of Auer rods
- No evidence of persisting leukemia by flow cytometry (Sensitivity: 5%)
- Absence of extramedullary leukemia
- Peripheral blood with no blast cells and less than 1,000/ $\mu$ l granulocytes irrespective of the platelet count
- Molecularly negative (no detection of pre-treatment genetic markers with a methodology providing a sensitivity of at least 1:10^3)

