### Treatment failure:

#### Partial Remission (PR):

- Platelet count  $>100,000/\mu\text{l}$
- Granulocyte count of  $>1,000/\mu\text{l}$
- Bone marrow (aspirate with marrow spicules): Decrease of at least 50% in the percentage of blasts to 5% - 25%

Stable disease: Patient survives  $\geq 7$  days post Chemotherapy (CT); persistent AML in blood or bone marrow neither fulfilling the criteria of Partial Remission nor the criteria of disease progression

Disease progression: Patient survives  $\geq 7$  days post Chemotherapy (CT) with any of the following:

- Reappearance of blasts in the peripheral blood or
- raising blast counts in the peripheral blood or
- raising blast counts in bone marrow or
- appearance, reappearance or progression of chloromas, or
- raising lactate dehydrogenase serum level not otherwise explained,

evaluated as significant disease progression by the investigator.

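### The two definitions of the primary ORR disagree on a patient with <5% marrow blasts and recovered neutrophils and platelets who still needs red-cell transfusion: no response category under 8.4.1 and 8.5, CR under the 3.2.2 footnote

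*Protocol*

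**What the plan says.** Section 3.2.2 names ORR (CR, CRp and CRi) as the Phase II primary endpoint and defines the three terms in a footnote. CR there is "less than 5% bone marrow blasts and regeneration of both peripheral neutrophils to" above 1,000/µl, with platelets above 100,000/µl. Hemoglobin and transfusion are not mentioned.

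Section 8.4.1 defines the terms again. CR needs platelets above 100,000/µl, granulocytes above 1,000/µl, the marrow, flow-cytometry and extramedullary conditions, and a "Transfusion independent stable hemoglobin value". CRp needs granulocytes above 1,000/µl and "Peripheral blood with no blast cells and less than 100,000" platelets per µl. CRi needs granulocytes below 1,000/µl at any platelet count. Neither CRp nor CRi has a hemoglobin condition. PR asks for a "Decrease of at least 50% in the percentage of blasts to 5% - 25" per cent, and stable disease presupposes that AML persists.

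Section 8.5 defines ORR as the share of patients reaching CR, CRp or CRi under those criteria at any time in the study.

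Section 5.4.1 uses the same three terms to decide on further cycles. One of its conditions is "III. no adequate response (CR, CRp or CRi) in the bone marrow evaluation between days 24 and 28".

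**The concern.** Adding a hemoglobin condition to CR alone leaves a hole in 8.4.1. A patient whose marrow is clear and whose neutrophils and platelets have both recovered, but who is still red-cell transfused, fails CR on hemoglobin, CRp because platelets are too high, and CRi because granulocytes are too high. The 3.2.2 footnote has no such hole and classifies this patient as CR.

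The number of responders in the primary analysis can therefore depend on which section is read, and the protocol does not say which one governs. An analysis plan written from it inherits two incompatible definitions. Under 8.4.1 the endpoint is also not ordered: among transfused patients, better platelet recovery can turn a response into a non-response at that assessment.

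**Working it through.** **1. Classification.** Take a patient who meets every marrow, flow-cytometry and extramedullary condition, has no blood blasts, and is red-cell transfused.

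| Granulocytes | Platelets | 8.4.1 | 3.2.2 footnote |
|---|---|---|---|
| >1,000/µl | >100,000/µl | none | CR |
| >1,000/µl | <100,000/µl | CRp | CRp |
| <1,000/µl | any | CRi, if also molecularly negative | CRi |

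If the patient is transfusion independent, the first row is CR under both sections. The hemoglobin line alone therefore creates the gap in that row.

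**2. The remaining categories of 8.4.1.** PR fails because blasts are below 5%. Stable disease fails because AML does not persist. Progression, early death, an unevaluable marrow and an incomplete first course do not describe this patient. The patient is unclassified, and 8.5 counts no response at that assessment.

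**3. Ordering.** Hold transfusion need fixed and move platelets from below to above 100,000/µl. Under 8.4.1 the patient goes from CRp to no category; under the footnote, from CRp to CR.

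**4. Who is lost.** Section 8.5 accepts a response at any time. A patient who later becomes transfusion independent, or who is CRp at another assessment, is still a responder. Only a patient who fits no category at every assessment is lost.

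**5. The plan's own figure.** Section 8.1 sets a 25% null ORR, "tested against a one-sided alternative on the significance level" 0.025, 80% power and an expected ORR of 0.50 × 0.13 + 0.35 × 0.87 = 0.3695, stated as 37%. With the normal approximation,

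n = [(1.960 × √(0.25 × 0.75) + 0.842 × √(0.3695 × 0.6305)) / 0.1195]² = 110.3,

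which rounds up to 111, as stated. Adding 11 gives 122.

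**6. Illustration of sensitivity.** The primary test in 8.2 is exact binomial on all included patients. At n = 122 it rejects at 41 or more responders (actual alpha 0.0206). At n = 111 it rejects at 38 or more (0.0186). At 37%, 122 × 0.37 = 45.1 responders are expected, about four above the cut-off. Two assumptions follow, neither of them in the protocol: that the 37% counts the patients in question, and that the stated number of percentage points is permanently lost.

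| Points lost (assumed) | ORR | Power, n = 122 | Power, n = 111 |
|---|---|---|---|
| 0 | 37% | 80.7% | 75.7% |
| 1 | 36% | 73.9% | 68.4% |
| 2 | 35% | 65.9% | 60.2% |
| 3 | 34% | 57.0% | 51.5% |
| 5 | 32% | 38.4% | 34.0% |

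One point of 122 is 1.2 patients. The table shows how sensitive the test is to small changes in the count; it does not estimate the effect.

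**7. Continuation wording.** Read literally, 5.4.1 treats the unclassified patient as having no adequate response, which points to a further cycle if its other conditions hold. Sections 5.4.2 and 5.4.3 continue treatment for partial remission or stable disease, and this patient has neither. Section 5.4.4.2 says further cycles go only to patients whose leukemia persists. These texts do not agree for this patient.

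**The case against.** The strongest reply is that the primary endpoint is first stated in 3.2.2, where the patient is a CR, so nothing is lost. That blocks a reader from inferring that the trial definitely counts this patient as a non-responder. It does not remove the defect, because 8.5 defines ORR through the 8.4.1 criteria and the two sections still conflict.

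Several stronger readings are tempting, and the protocol does not support them:

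- **The patient automatically gets another cycle.** Sections 5.4.2, 5.4.3 and 5.4.4.2 point the other way, and 5.4.1 itself lets the investigator postpone. Only a disagreement between passages is shown.
- **A further cycle would renew the cytopenia and cost the response.** If the marrow stays clear and platelets alone fall below 100,000/µl, the patient becomes CRp and is counted. Loss would need relapse, for which the protocol offers no evidence.
- **The single evaluation on days 24 to 28 cannot show a stable hemoglobin, so the response is lost.** Later assessments can supply it, because 8.5 accepts a response at any time.
- **The patient is in a better remission than any CRp patient.** This holds only against a CRp patient with the same transfusion need; CRp patients may be transfusion independent.
- **Power falls by a known amount.** The protocol gives no share of such patients, and 8.1 does not say which definition lies behind 25% or 37%. If both already follow 8.4.1, there is no loss against plan.

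It is also fair to say that 8.4.1 claims to follow the revised International Working Group recommendations. These are not at hand, so whether dropping the hemoglobin line would depart from them cannot be checked here. The footnote claims the same origin, so that does not settle which section governs.

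**Conclusion.** The point stands as a contradiction in the definition of the primary endpoint. For a patient with <5% blasts, both counts recovered and continued red-cell transfusion, 8.4.1 with 8.5 gives no response at that assessment, while the 3.2.2 footnote gives CR. Under 8.4.1 the ordering is also reversed against an equally transfused patient with low platelets.

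On this row, reading 8.4.1 instead of the footnote can only lower ORR or leave it unchanged. Losses are confined to patients who never meet a category. How many there would be cannot be derived from the protocol, and the power figures above are illustrations on assumed losses. The case for correction is that the primary responder count should not depend on which section is read, and that the change is cheap.

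**What to change.** Make one definition govern, and have 3.2.2, 8.4.1 and 8.5 all refer to it. Make the ORR categories exhaustive: for the ORR endpoint, a patient with <5% blasts, the other marrow, flow-cytometry and extramedullary criteria met and both counts recovered is a responder regardless of red-cell transfusion. If transfusion independence is wanted, keep it as a qualifier when the CR rate is reported.

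Three small items belong in the same edit. State in 8.1 that the 25% and 37% refer to the governing definition. Assign counts of exactly 1,000/µl and 100,000/µl, which both sections leave without a category at the boundaries between CR, CRp and CRi. Settle whether CRi requires molecular negativity, which 8.4.1 lists and the footnote does not.

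The response term in 5.4.1 and the continuation wording in 5.4.2, 5.4.3 and 5.4.4.2 must be reconciled by the sponsor. No clinical rule is proposed here; the text above concerns only the counting of ORR.

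Cost: a wording amendment with no change to the sample size and no new procedures for ORR. The CR rate will need a note on transfusion status. If that qualifier is kept, check that red-cell transfusions are recorded, since Table 2 in 6.2 does not list them.

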#### Morphologic relapse:

- Reappearance of blasts post CT in PB or bone marrow

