#### Overall response rate (ORR):

Proportion of patients who achieve either a complete remission (CR), a CRp or a CRi, as defined above, at any time point during study participation.

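### The CR criteria in 8.4.1 omit the blast-free blood condition that CRp and CRi carry, so CR, and with it the primary ORR, can include a patient with circulating blasts

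*Protocol*

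**What the plan says.** Section 8.4.1 lists the conditions for each responder category.

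- **CR** has six items. The first is "Platelet count >100,000" per µl. Then come granulocytes above 1,000/µl, marrow blasts below 5% without Auer rods, a negative flow cytometry finding, no extramedullary leukemia and, last, "Transfusion independent stable hemoglobin value".
- **CRp** repeats the granulocyte, marrow, flow and extramedullary items and adds "Peripheral blood with no blast cells and less than 100,000" platelets per µl.
- **CRi** repeats the marrow, flow and extramedullary items, adds "Peripheral blood with no blast cells and less than 1,000" granulocytes per µl, and also asks for molecular negativity.

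The blood items of CRp and CRi thus share the opening "Peripheral blood with no blast cells and less than", followed by their own count; CR has no counterpart.

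The flow item is the same in all three lists: "No evidence of persisting leukemia by flow cytometry (Sensitivity: 5" (the 5 is a percentage). It does not say whether marrow or blood is tested.

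The footnote in 3.2.2 summarises the three categories by marrow blasts, neutrophils and platelets. It mentions blood blasts for none of them.

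Later in 8.4.1, stable disease is a form of treatment failure that includes AML persisting in the blood. Morphologic relapse is "Reappearance of blasts post CT in PB or bone marrow", with no minimum level. Section 8.5 defines the ORR as "Proportion of patients who achieve either a complete remission (CR), a CRp or a CRi, as defined above", reached at any time during participation.

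**The concern.** The ORR is the primary endpoint of phase II, and 8.5 takes it directly from the 8.4.1 lists. Two of the three responder categories exclude circulating blasts and CR does not, with no reason given. Two patients who differ only in platelet count can therefore fall on opposite sides of the primary endpoint although both have blasts in the blood.

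The CR patient may also satisfy a failure category or the relapse definition at the same assessment, and the protocol gives no order of precedence. The label matters beyond the ORR. It feeds the CR rate and entry into the RFS analysis. Under 5.4.1 and 5.4.3 it also decides between observation and further cycles, so those sections depend on reconciled lists.

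The missing condition works in one direction: it can turn a non-responder into a responder but never the reverse. In a single-arm test against a fixed 25% there is no control arm in which the same leniency would cancel out.

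**Working it through.** **1. The lists side by side (8.4.1)**

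| Item | CR | CRp | CRi |
|---|---|---|---|
| Platelets (/µl) | >100,000 | <100,000 | any |
| Granulocytes (/µl) | >1,000 | >1,000 | <1,000 |
| Marrow blasts <5%, no Auer rods | yes | yes | yes |
| Flow negative (5% sensitivity) | yes | yes | yes |
| No extramedullary leukemia | yes | yes | yes |
| Transfusion-independent hemoglobin | yes | – | – |
| Molecularly negative | – | – | yes |
| **No blasts in blood** | **–** | **yes** | **yes** |

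**2. Two constructed patients**

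Both have 4% marrow blasts without Auer rods, negative flow, granulocytes 1,500/µl, stable hemoglobin without transfusion, no extramedullary disease and 2% blasts in the blood.

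- Patient A has platelets of 120,000/µl. All six CR items are met, so A is a CR and an ORR responder.
- Patient B has platelets of 90,000/µl. The blood item of CRp fails, so B is not a responder. By the 3.2.2 footnote, which has no blood item, B would be a CRp.

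**3. What else patient A can meet**

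- *Blasts never cleared.* There is no reappearance, so relapse is not met. If the blasts count as persisting AML, stable disease is: its definition sets aside patients who meet partial remission or progression, but not those who meet CR. Partial remission does not apply, because it needs 5–25% marrow blasts.
- *Blasts cleared and returned.* Morphologic relapse is met at the assessment that meets CR. The progression definition has a similar blood item, but it also needs the investigator to judge the progression significant.

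**4. Does another CR item close the gap?**

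The flow item may exclude some such patients. Its 5% sensitivity and unnamed compartment leave room for others. The protocol lists the same item for CRp and CRi and still adds the blood condition there, so it does not treat flow as a substitute.

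**5. The plan's own sample size (8.1), as background**

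Expected ORR = 0.50 × 0.13 + 0.35 × 0.87 = 0.3695. Normal approximation:

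n = [(1.960 × √(0.25 × 0.75) + 0.842 × √(0.3695 × 0.6305)) / 0.1195]² = 110.3, rounded up to 111. Adding 11 gives 122. The plan's figures are reproduced.

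**6. Size per patient**

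Section 8.2 applies the exact binomial test by intention to treat, so n = 122 is used. At one-sided 0.025 the test rejects at 41 or more responders (exact level 0.0206). One patient moves the ORR by 1/122 = 0.82 points.

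**7. Possible frequency (assumed)**

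Assume that half of responders are CR and that 1–5% of CR patients have circulating blasts. Neither figure is in the protocol.

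- At the expected ORR: 122 × 0.37 ≈ 45 responders, about 22 CR, so 0.2 to 1.1 patients, or about 0.2 to 0.9 points.
- At the null: 122 × 0.25 = 30.5 responders, about 15 CR, so 0.15 to 0.76 patients, or about 0.1 to 0.6 points.

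For scale, if the true ORR were 25% and such patients added a full 1 point, the chance of a false positive would rise from 2.1% to 3.8%; with 2 points it would be 6.4%. Both lie above the assumed range at the null.

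**The case against.** The strongest reply is that this is a drafting slip with little practical reach. The patient in question has recovered granulocytes and platelets, transfusion-independent hemoglobin, a marrow below 5% and negative flow, yet blasts in the blood. Nothing in the protocol shows that this combination occurs with any frequency. Section 8.4 says that blood differentials are used to assess efficacy, stable disease already offers a failure category for persisting leukemia in blood, and 8.4.1 refers to published response criteria that may contain the condition.

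The point about rarity stands. The rest does not repair the text. No CR item uses the differential. The stable-disease category creates an overlap rather than resolving one. The cited standard is not at hand, and 8.5 ties the endpoints to the definitions written in the protocol.

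Some stronger readings are tempting, but the documents do not support them.

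- *Every patient with circulating blasts is both CR and relapsed on one blood count.* CR also needs the marrow, flow, extramedullary and hemoglobin items, and relapse needs blasts to reappear after clearance.
- *Such patients enter RFS with an event at time zero.* Section 8.5 starts RFS when a leukemia-free state is first achieved, which hardly describes a patient with leukemic blasts in the blood. Where blasts never cleared there is no relapse event either.
- *CR is meant to be the strictest category, so the omission must be an error of rank.* The protocol does not say so, and the lists are not nested: only CRi asks for molecular negativity.

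**Conclusion.** The omission is real and sits in the definition of the primary endpoint. As written, CR can include a patient with circulating blasts whom CRp and CRi would exclude, and that patient can also meet stable disease (blasts persisting) or morphologic relapse (blasts returned after clearance), with no rule to decide between them.

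The bias runs only towards more responders. A later confirmatory marrow (6.1.4) does not undo a response, because 8.5 counts a response at any time.

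The effect is 0.8 points of ORR and of the CR rate per patient at n = 122. The number of patients rests on assumption. With 1–5% of about 22 CR patients affected it is about one at most, and it may be none. One patient could decide a result at the boundary of 41 responders, but that is true of any misclassification in an exact test and does not by itself make the point large. The point deserves correction because the endpoint rule contradicts itself and the correction is nearly free.

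**What to change.** Add to the CR list in 8.4.1 the requirement that the peripheral blood contain no blasts, worded as for CRp and CRi. Put the same condition in the 3.2.2 footnote for all three categories. CR, CRp and CRi then share one blood condition and no longer overlap with stable disease through persisting blood blasts, or with relapse through returning ones. The places in 5.4.1 and 5.4.3 that rely on the response label should be read against the reconciled lists.

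The cost is one line in 8.4.1 and a short addition to the footnote. The differential blood count is already taken at each response evaluation (5.4.1), so no new assessment is needed. The CR rate and ORR may come out slightly lower.
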